## Abstract

**Introduction::**

The aim of the present study is to compare the microcirculatory difference of different meridians by using laser doppler flowmetry and investigate the specificity for the meridian-visceral association and site-to-site association between 2 specific meridians.

**Methods and analysis::**

The Lung and Heart meridians are chosen as 2 specific studied meridians. 120 participants will be enrolled and divided into the healthy control group, chronic stable angina pectoris group and healthy intervention group. Laser doppler flowmetry will be used to assess the blood perfusion of the Heart and Lung meridians. The specificity for the meridian-visceral association will be investigated by comparing the microcirculatory difference between the Heart and Lung meridians in the healthy control group and chronic stable angina pectoris group. Besides, participants in the healthy intervention group will receive 2 sessions of moxibustion in the Heart meridian and Lung meridian, respectively, to explore the specificity for the site-to-site association on the body surface. Primary outcomes will be blood flow curve and blood perfusion units of relevant sites along the Heart and Lung meridians. Statistical analysis will be conducted by third party statisticians.

**Ethics and dissemination::**

Ethics approval (approval No: ZSLL-KY-2019-001A-01) has been obtained from the Ethics Committee of the Third Affiliated Hospital of Zhejiang Chinese Medical University. The study findings will be disseminated through presentation at peer-reviewed medical journals.

**Trial registration::**

ClinicalTrials.gov NCT04244812.

## Introduction

1

In recent years, acupuncture has received increasing attention in many Western countries. Convincing evidence based on meta-analyses has proved that acupuncture is effective for treating a wide range of diseases, such as pain conditions,^[1,2]^ respiratory diseases,^[3,4]^ cardiovascular disorders^[5,6]^ and digestive diseases.^[7,8]^ Although acupuncture gains increasing acceptance, as the guidance of almost all acupuncture clinical practices for thousands of years,^[9]^ the existence of meridian systems and meridian theory have been questioned.^[10,11]^

According to the theories of acupuncture and traditional Chinese medicine, meridians distribute on the surface of the whole body vertically and horizontally, integrating the surface of the body with internal organs, thus transforming the whole body into one entire organ.^[12]^ That is to say, the essence of the meridian theory and meridian systems mainly manifests its summaries concerning the fundamental rules for correlation and specificity of different sites of the body. After many years of effort, although the physical structure of meridians has not been found, the biological characteristics of meridians has been confirmed,^[9]^ which could be used as the entry point for meridian studies. However, the majority of the existing studies involve lots of subjective assessments. Moreover, few studies have investigated the site specificity between 2 specific meridians.

Therefore, the present study adopts laser doppler flowmetry (LDF) to assess the microcirculatory characteristics of meridians, which is an established approach for monitoring blood flux in the microcirculation^[13]^ with advantages of non-invasiveness, measurement of rapid response, ease of application, continuity, and tissue specificity.^[14]^

The aim of the present study is to compare the difference in the microcirculatory characteristics of 2 specific meridians. Specifically, the specificity for the meridian-visceral association and site-to-site association between 2 specific meridians will be investigated. The Heart and Lung meridians are chosen as the 2 studied meridians. Thus, patients with chronic stable angina pectoris (CSAP) and healthy adults will be included. The findings of this study will provide evidence for the biological basis of meridians and bring important reference for the acupoint selection in acupuncture clinical practice.

## Methods and design

2

### Study design

2.1

We will conduct a prospective and clinical controlled trial. All participants will be divided into the healthy control group, CSAP group and healthy intervention group. The standard protocol items including Recommendations for Interventional Trials and the Standards for Reporting Interventions in Clinical Trials of Acupuncture guidelines will be followed during the development of this trial protocol. The study design flowchart is shown in Figure 1 and the schedule of enrolment, interventions and assessments is displayed in Table 1.

**Figure 1 F1:**
[figure not shown]
Study design flowchart. CSAP = chronic stable angina pectoris.

**Table 1 T1:**
[figure not shown]
Trial schedule of enrollment, intervention and assessments.

### Sample size estimation

2.2

This trial is a meridian study that uses a modern technique to assess the biological characteristics of meridians. Compared with general clinical trials, there is no unified standard for the sample size estimation. Based on similar meridian studies,^[15–17]^ a total of 120 participants will be included and divided into the healthy control group, CSAP group and healthy intervention group, with 40 subjects in each group respectively.

### Participants

2.3

The subjects of this study include healthy adults and CSAP patients.

#### Inclusion criteria

2.3.1

##### Inclusion criteria for healthy adults

2.3.1.1

(1)Healthy adults should provide a recent medical examination report to confirm they have not any cardiovascular, respiratory, digestive, urinary, hematological, endocrine, and neurological disease;(2)Age ≥20 years, male or female;(3)Participants have clear consciousness and could communicate with others normally;(4)Participants could understand the full study protocol and written informed consent is signed.

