##### Inclusion criteria for the CSAP patients

2.3.1.2

(1)Patients should meet the diagnostic criteria of coronary heart disease, which includes the following items: 1) confirmed old myocardial infarction, or a history of percutaneous coronary intervention, or coronary artery bypass grafting; 2) 50% or more luminal stenosis in at least one coronary artery or major branch segment confirmed by coronary angiogram or CT angiography; 3) myocardial ischemia indicted by exercise stress radionuclide myocardial imaging; 4) treadmill exercise testing is positive;(2)Patients should meet the diagnostic criteria of CSAP and the Canadian Cardiovascular Society classification for CSAP is level II or III;(3)The medical history of CSAP is more than 3 months with attacks occurring at least twice weekly in the last month;(4)35≤age≤75 years, male or female;(5)Patients have clear consciousness and could communicate with others normally;(6)Patients could understand the full study protocol and written informed consent is signed.

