### Recruitment procedures

2.4

This trial will be performed at the Third Affiliated Hospital of Zhejiang Chinese Medical University. A total of 120 participants will be recruited through posters and networks. All participants will be informed of the purpose, contents, benefits and potential risks of the study. And the written informed consent will be signed.

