#### Concomitant treatments

2.6.3

During the study period, all the participants in the CSAP group will maintain their previous treatment regimen. If additional medications or other treatments are used during the study period due to any reasons, the details (eg, the name, administration time and dosage of the medication) should be documented.

Besides, participants in the healthy control group and healthy intervention group should not take any medications during the full study period. If drugs or other treatments are adopted due to sudden diseases, researchers will evaluate whether they should be withdrawn from the study.

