### Data collection and statistical analysis

2.10

Statistical analysis will be performed using the statistical software package SPSS 17.0 for Windows (SPSS Inc., Chicago, IL) by third party statisticians who does not participant in this trial. Numeric data with normal distribution will be expressed as mean ± standard deviations, whereas data with skewed distribution as median with 95% confidence intervals. Categorical data will be shown as counts and percentages.

Repeated measures ANOVA will be used to assess change in continuous variables before and after intervention. The paired samples *t*-test will be used to compare the changes within the groups, whereas the independent samples t-test will be employed for comparisons between the groups. Within-group/between-group comparison regarding data with skewed distribution is assessed using non-parametric test. Between-group differences for baseline dichotomous variables, such as gender and ages, will be tested using the Chi-square test. A *P* value of less than .05 will be considered statistically significant.

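### Controls aged 20 or over are compared without adjustment with angina patients aged 35–75, so an age difference can appear as a disease effect in the raw group comparison

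*Protocol article*

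**What the plan says.** All of this is in the protocol article.

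- **Eligibility.** Healthy adults (section 2.3.1.1): "Age ≥20 years, male or female". CSAP patients (section 2.3.1.2): "35≤age≤75 years, male or female".
- **Group formation.** Section 2.1: "All participants will be divided into the healthy control group, CSAP group and healthy intervention group". Section 2.2 sets the size, "with 40 subjects in each group respectively". Section 2.4 gives the route: "A total of 120 participants will be recruited through posters and networks". None of these sections mentions matching or balancing on age.
- **Analysis.** Section 2.10 assigns between-group comparisons to the independent-samples t-test, or to a non-parametric test for skewed data, and names no covariate. On age it says: "Between-group differences for baseline dichotomous variables, such as gender and ages, will be tested using the Chi-square test". It gives no cut-point for age and no consequence if the groups differ.
- **Control of confounding.** Section 2.6 lists room conditions, time of day, intake, smoking and exercise. Age is not listed.
- **Use of the comparison.** The Discussion (section 3) uses healthy controls versus CSAP patients for two purposes. One is to show sensitisation of meridians in disease. The other is to show that the group difference is larger on the Heart than on the Lung meridian.

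**The concern.** Membership of the CSAP group follows from disease, so randomisation cannot balance age against the controls. The eligibility rules also let age differ: the floor for controls is 15 years lower, and they have no ceiling. Controls aged 20–34 have no counterpart among the patients.

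If skin perfusion varies with age, an unadjusted test at any one site mixes age with disease. The chi-square test does not prevent this. Age is continuous, so dichotomising it discards information, and a baseline p-value leaves any imbalance in the outcome comparison whatever it shows. At stake is the sensitisation claim, which rests on the raw difference between the groups.

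**Working it through.** **The plan's own figure.** Section 2.2 gives 120 participants, and 3 × 40 = 120 agrees. It states no effect size, SD or power, so the number cannot be reproduced further. For scale, the difference detectable with 80% power at two-sided 5% is (1.960 + 0.842) × √(2/40) = 2.802 × 0.2236 = 0.63 SD.

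**Inputs from the article.** n = 40 per group; significance level 0.05 (two-sided assumed, as sidedness is not stated); age ranges ≥20 and 35–75.

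**Assumed inputs.** The documents give neither an age-perfusion slope nor the ages to be enrolled. I take a slope *b* of 0.1 to 0.2 SD per decade and a gap *g* in mean age of 7.5, 15 or 20 years. The 7.5-year gap is what uniform ages give if controls are capped at 75 for the calculation: (35 + 75)/2 − (20 + 75)/2 = 55 − 47.5 = 7.5.

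**Formula.** With no disease effect, the spurious standardised difference is d = b × g/10. The t statistic then has 78 degrees of freedom and noncentrality d/√(2/40) = 4.472 × d. The false-positive rate is the probability that it falls beyond the two-sided 5% limits.

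| Gap in mean age | d at b = 0.1 | Rate | d at b = 0.2 | Rate |
|---|---|---|---|---|
| 7.5 years | 0.075 | 6.3% | 0.15 | 10.2% |
| 15 years | 0.15 | 10.2% | 0.30 | 26.3% |
| 20 years | 0.20 | 14.3% | 0.40 | 42.4% |

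**Simulation check** (5,000 runs per setting, 40 per group, no disease effect). Controls uniform on 20–75 against patients uniform on 35–75 gave 6.4% and 9.9% for the unadjusted t-test at the two slopes, in line with the first row.

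**Effect of the remedies**, for slopes of 0.1 to 0.3 SD per decade:

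- A linear model with continuous age gave 4.6% to 5.3%. The simulated age effect was linear, so the model was correctly specified by construction.
- The same 35–75 range and distribution in both groups gave 4.9% to 5.4%, even unadjusted.
- A t-test on the within-person Heart-minus-Lung difference gave 4.5% to 5.5% when age acted equally on both meridians.

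**Is that contrast in the plan?** Section 2.6.1 measures two Heart and two Lung sites in every control and CSAP participant, so the contrast can be computed. Section 2.10 reserves repeated-measures ANOVA for change before and after intervention. The control-versus-CSAP comparison involves no intervention, so no test of group by meridian is named for it.

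**The case against.** The strongest reply is that the stated hypothesis is a Heart-versus-Lung contrast within the same person, in which any age effect common to both meridians cancels. This stands, and it limits the finding. The rates in the table apply to single-site group tests, not to a properly tested contrast. A reader might infer that the meridian-visceral hypothesis is itself biased by age. That would require age to act differently on the two meridians, and the documents say nothing either way. What remains is that section 2.10 names no test of the contrast, and that the sensitisation claim uses the raw group difference.

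The size is also assumption. A reader might infer far higher error rates: controls aged 20–40 against patients aged 50–75 satisfy the criteria, and the simulation then gives 29% and 82% at the two slopes. Nothing in the article shows that such samples are expected. Poster recruitment and the requirement that "they have not any cardiovascular, respiratory, digestive, urinary, hematological, endocrine, and neurological disease" may favour younger controls, but that is inference, and with no upper limit some controls could be older than any patient.

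A reader might add drugs and comorbidity as further errors, since "all the participants in the CSAP group will maintain their previous treatment regimen" while healthy participants take no medication, and endocrine disease is not named among the CSAP exclusions. The drug difference is inherent in comparing patients with healthy people. The exclusion for serious concomitant conditions in section 2.3.2.2 gives its organ systems as examples, so an unnamed system is not thereby admitted. Both belong among the limitations.

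Finally, matching or adjustment may be set out in a full protocol or SAP that is not shown, so it cannot be said that no other safeguard exists. The finding rests on what the article fixes: unequal age criteria, a named unadjusted test and a mistyped age variable. Its pilot status and general call for caution (section 3) do not name age.

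**Conclusion.** The point holds for the raw control-versus-CSAP comparison. If the article is followed as written, an age difference can be reported as a disease effect and read as sensitisation. Under an assumed slope of 0.1–0.2 SD per decade with 40 per group, the nominal 5% error of a single-site t-test becomes about 6–10% for uniform ages over the permitted ranges (controls capped at 75), 10–26% at a 15-year gap and 14–42% at a 20-year gap. The inflation is slight if the groups turn out close in age and substantial if they do not, and the eligibility rules do not decide which.

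The Heart-minus-Lung contrast is protected against an age effect shared by both meridians, provided that it is actually tested. The moxibustion comparison is within person and much less exposed.

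**What to change.** 1. **Eligibility.** For the healthy control group only (the group measured at the same four sites as the CSAP patients), set the age range to 35–75 for remaining recruitment. Balance frequencies to the CSAP group on age band and sex where feasible.
2. **Group comparison.** Replace the unadjusted test with a linear model containing group, continuous age and sex. For controls already enrolled at ages outside 35–75 the adjustment relies on extrapolating the age slope, so also report the result without them.
3. **Meridian-visceral hypothesis.** Test the group-by-meridian term: for example, regress each participant's Heart-minus-Lung difference on group, age and sex. The age term then also allows for a different age slope on the two meridians.
4. **Baseline table.** Describe age as a continuous variable, by mean and SD or by median if skewed, and drop its chi-square test.
5. **Limitations.** State that concomitant drugs and comorbidity remain uncontrolled differences between the groups.

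**Cost.** A protocol amendment in an ongoing trial, a control group enrolled under two age rules, somewhat slower recruitment of older healthy volunteers, and two degrees of freedom (78 to 76 with 80 participants). Age and sex are already to be compared at baseline, so no new data are needed.

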##### Inclusion criteria for the CSAP patients

2.3.1.2

(1)Patients should meet the diagnostic criteria of coronary heart disease, which includes the following items: 1) confirmed old myocardial infarction, or a history of percutaneous coronary intervention, or coronary artery bypass grafting; 2) 50% or more luminal stenosis in at least one coronary artery or major branch segment confirmed by coronary angiogram or CT angiography; 3) myocardial ischemia indicted by exercise stress radionuclide myocardial imaging; 4) treadmill exercise testing is positive;(2)Patients should meet the diagnostic criteria of CSAP and the Canadian Cardiovascular Society classification for CSAP is level II or III;(3)The medical history of CSAP is more than 3 months with attacks occurring at least twice weekly in the last month;(4)35≤age≤75 years, male or female;(5)Patients have clear consciousness and could communicate with others normally;(6)Patients could understand the full study protocol and written informed consent is signed.

#### Exclusion criteria

2.3.2

##### Exclusion criteria of the healthy adults

2.3.2.1

(1)Participants have mental illness, severe depression, alcohol dependence or history of drug abuse;(2)Pregnant or lactating participants;(3)Participants are participating in other trials.

##### Exclusion criteria for the CSAP patients

2.3.2.2

(1)Patients have acute coronary syndrome and severe arrhythmias;(2)Patients’ chest pain is caused by valvular heart disease, hypertrophic cardiomyopathy and dilated cardiomyopathy;(3)Patients’ chest pain is caused by non-cardiac disease;(4)Patients have concomitant lung diseases, such as obstructive pulmonary disease;(5)Patients have serious concomitant conditions and fail to treat them effectively, such as diseases of the digestive, urinary, respiratory, haematological, and nervous system;(6)Patients have mental illness, severe depression, alcohol dependence or history of drug abuse;(7)Pregnant or lactating patients;(8)Patients are participating in other trials.

### Recruitment procedures

2.4

This trial will be performed at the Third Affiliated Hospital of Zhejiang Chinese Medical University. A total of 120 participants will be recruited through posters and networks. All participants will be informed of the purpose, contents, benefits and potential risks of the study. And the written informed consent will be signed.

### Blinding

2.5

This is an open-labeled controlled trial. The participants, manipulators and outcome assessors will not be blinded. In the data analysis stage, statistical analysis will be conducted by third party statisticians who are blinded to the study protocol.

### Experimental procedures

2.6

All participants in 3 groups will receive examination of LDF. Besides, participants in the healthy control group will receive moxibustion intervention in the Heart and Lung meridians successively.

To minimize the interference effect induced by confounding factors, all LDF examinations will be performed in a quiet experimental room, controlled for temperature and humidity (24°C ± 1°C; relative humidity 30%–40%), in the morning at about the same time of day. All subjects will be refrained from consuming coffee, tea, alcohol, or smoking cigarettes on the examination day. Exercise and food will also be restricted at least 1 hour before experiment.

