#### Procedures for LDF examination and moxibustion

2.6.1

A four-channel LDF (PeriFlux System 5000, Sweden) will be used to measure the microcirculatory characteristics of the Heart and Lung meridians, which could monitor 4 measurement sites simultaneously. The participants will be asked to stabilize for 15 minutes in a supine position in the experimental room before LDF examination. They will be informed to keep silent and normal breath and avoid limb movement during the whole measurement period. The probes will be placed at corresponding measurement sites. Blood flow curve and microcirculatory flux, expressed as blood perfusion units (PU), will be assessed.

(1)Healthy control group and CSAP groupThe probes will be left at 4 measurement sites (Fig. 2), which include “Shenmen” (HT7) and “Shaohai” (HT3) of the Heart meridian, “Taiyuan” (LU9) and “Chize” (LU5) of the Lung meridian. The blood flow curve and PU will be recorded for 5 minutes.(2)Healthy intervention groupTwo sessions of moxibustion will be performed in the Heart meridian and Lung meridian, respectively. The washout period between the two sessions is at least one day to avoid inter-experiment interference. The intervention procedures and LDF measurement sites are shown in Figure 3.

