**Figure 3 F3:**
[figure not shown]
The intervention procedure of the healthy intervention group. (A) Moxibustion site of the Heart meridian and LDF measurement sites of the Heart and Lung meridians; (B) Moxibustion site of the Lung meridian and LDF measurement sites of the Heart and Lung meridians. CSAP = chronic stable angina pectoris, LDF = laser doppler flowmetry.

(1)Intervention in the Heart meridian: By igniting the moxa stick and inserting it into a homemade moxibustion holder to adjust appropriate angle and height, moxibustion will be performed at “Shaohai” (HT3) of the Heart meridian for 15 minutes. During moxibustion, LDF probes will be placed in three measurement sites, which include the midpoint of the Heart meridian along the left forearm (ie, midpoint of between HT3 and HT7), “Chize (LU5)” of the Lung meridian, and the midpoint of the Lung meridian along the left forearm(ie, midpoint of between LU5 and LU9). The intervention procedure and LDF measurement sites are shown in Figure 3 (A). The measurement time points include 5 minutes before moxibustion, 15 minutes during moxibustion and 5 minutes after removal of moxibustion.(2)2)Intervention in the Lung meridian: The moxibustion acupoint is “Chize” (LU5) of the Lung meridian. The LDF examination, moxibusition procedure and measurement time points are the same as 1). During moxibustion, the LDF probes will detect the blood perfusion in three measurement sites, which include the midpoint of the Lung meridian along the left forearm(i.e. midpoint between LU5 and LU9), “Shaohai” (HT3) of the Heart meridian, and the midpoint of the Heart meridian along the left forearm (i.e. midpoint between HT3 and HT7. The intervention procedure and LDF measurement sites are shown in Figure 3(B).

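### The order of the two moxibustion sessions is neither randomised nor counterbalanced; if it is Heart then Lung, as worded, session cannot be separated from stimulated meridian in between-session comparisons

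*Protocol article*

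**What the plan says.** One group of 40 healthy participants receives moxibustion. The Abstract and section 2.6.1 call it the healthy intervention group; section 2.6 and the Discussion call it the healthy control group.

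On sequence, section 2.6 says that this group "will receive moxibustion intervention in the Heart and Lung meridians successively". Section 2.6.1 lists the Heart session as item 1, where "moxibustion will be performed at “Shaohai” (HT3) of the Heart meridian for 15 minutes", and the Lung session as the second item: "The moxibustion acupoint is “Chize” (LU5) of the Lung meridian". Between them, "The washout period between the two sessions is at least one day to avoid inter-experiment interference". No section states that the order is randomised, alternated or counterbalanced.

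Each session uses three probes. In the Heart session they sit on the Heart midpoint and on "Chize (LU5)” of the Lung meridian, and the midpoint of the Lung meridian along the left forearm". In the Lung session the sites are "midpoint between LU5 and LU9), “Shaohai” (HT3) of the Heart meridian, and the midpoint of the Heart meridian along the left forearm". Each session is recorded for 5 minutes before, 15 minutes during and 5 minutes after moxibustion.

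The Discussion hypothesises a larger change at sites of the stimulated meridian than at sites of the non-stimulated one. Section 2.10 names repeated-measures ANOVA and paired and independent t-tests.

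**The concern.** The two sessions form a within-person comparison, and in such a design the order of sessions is part of the design. If everyone has Heart first, whatever distinguishes a first session from a second (unfamiliar heat, habituation, a changed skin response after earlier heating) always coincides with the change of stimulated meridian. The trial is open-label for participants, operators and assessors, so blinding does not limit such effects.

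The probe layout adds an asymmetry. In session 2 a non-stimulated probe sits on HT3, which was heated in session 1, possibly only a day earlier. Its counterpart in session 1 sits on LU5, which has not yet been heated. At stake is whether a difference reported as meridian specificity could be an order or carry-over effect, or whether carry-over could hide a real difference. Once all data are collected in one order, no analysis can repair this.

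**Working it through.** The plan gives no figure that depends on session order; the group size of 40 is set by analogy with similar studies. The check is therefore of the design structure.

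**Inputs.** 40 participants, two sessions, and the probe sites in section 2.6.1. Assumption: Heart then Lung for all 40.

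| Site | Session 1 (HT3 heated) | Session 2 (LU5 heated) |
|---|---|---|
| Heart midpoint | recorded, stimulated meridian | recorded, non-stimulated meridian |
| Lung midpoint | recorded, non-stimulated meridian | recorded, stimulated meridian |
| LU5 | recorded, not yet heated | heated |
| HT3 | heated | recorded, previously heated |

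Only the two midpoints are recorded in both sessions.

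**Step 1: session against stimulated meridian.** Session 1 is Heart for 40/40 and session 2 is Lung for 40/40. The two indicators have correlation 1.0, and a design matrix with intercept, session and stimulated meridian has rank 2 of 3. With 20 participants in each order, the correlation is 0.0 and the rank 3 of 3.

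**Step 2: midpoint changes from baseline.** Let T be the true effect of stimulating a site's own meridian, d the Lung-minus-Heart site difference, p a uniform session-2 effect, and c a carry-over on the response of the previously stimulated meridian's midpoint.

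- Session 1: Heart midpoint T; Lung midpoint d.
- Session 2: Heart midpoint p + c; Lung midpoint p + d + T.

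Within-session contrast, stimulated minus non-stimulated:

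- Session 1: T − d.
- Session 2: (p + d + T) − (p + c) = d + T − c.
- Average: T − c/2. The uniform effect p has cancelled; c has not.

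With illustrative values T = 5, d = 2, p = 3, c = 1, the contrasts are 3 and 6. Their average is 4.5 against a true 5.0.

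Same site, stimulated minus non-stimulated:

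- Lung midpoint: (p + d + T) − d = T + p = 8.
- Heart midpoint: T − (p + c) = T − p − c = 1.

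Both meridians have the same true effect of 5, yet they appear to differ by 2p + c = 7.

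**Step 3: what one order can estimate.** Two sessions by two midpoints give four cell means. Intercept, session, site and stimulated status use all four (rank 4 of 4), and adding carry-over gives rank 4 of 5. Stimulated status is then exactly the site-by-session interaction. If the Lung midpoint responds more by g in session 2 for reasons unrelated to stimulation, the averaged contrast shifts by g/2 and nothing in the data reveals it.

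**Step 4: HT3 and LU5.** Suppose all sites truly change equally, but HT3 responds less by k because it was heated before. The Lung-session contrast of Lung midpoint minus HT3 then shows +k of false specificity; a carry-over of opposite sign masks a true effect. LU5, recorded before it is heated, has no matching distortion.

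**Step 5: 20 participants in each order.** For Lung then Heart:

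- Session 1: Lung midpoint d + T = 7; Heart midpoint 0; contrast 7.
- Session 2: Heart midpoint p + T = 8; Lung midpoint p + d + c = 6; contrast 2.

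The average is again 4.5, so c/2 remains. But the same-site differences become (8 + 1)/2 = 4.5 at the Lung midpoint and (1 + 8)/2 = 4.5 at the Heart midpoint, so the false difference of 7 between meridians is gone. First-session data alone give (3 + 7)/2 = 5 = T. Second-session data give (6 + 2)/2 = 4 = T − c, so c can be estimated. The model with carry-over has rank 5 of 5. The shift from g is +g/2 in one order and −g/2 in the other, and cancels.

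**The case against.** The strongest reply has four parts.

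- **The order is inferred.** A reader might infer that the protocol fixes Heart first for every participant. It does not: the wording of section 2.6 and the numbering in section 2.6.1 point that way without being an allocation rule. Figures 1 and 3 and Table 1 could not be read for this review and might say more. This stands, and the result is conditional on the order. It does not dispose of the point, because an investigator who follows the text would run Heart then Lung.
- **The stated hypothesis is within-session.** A reader might infer that a session effect passes in full into the specificity test. It does not. Both meridians are recorded in the same session against a same-session baseline, and p cancels in step 2. A loss of reactivity common to all sites likewise creates no specificity where the meridians do not differ.
- **Carry-over is uncertain.** A constant residual elevation cancels in change from baseline; only an altered response does not. Its direction is unknown, and it could shrink the contrast as easily as inflate it. A reader might also infer that it can fall only on HT3, but session 2 also records both midpoints; HT3 is simply the one site that was directly heated. The plan sets a washout for this purpose, and nothing in the document shows effects lasting beyond a day.
- **Model terms belong in the SAP.** A session term or baseline comparison may be specified there, so its absence from the article is not held against the plan. The order itself is a design matter, and no model term can recover it from a single sequence.

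**Conclusion.** The point holds in a limited form. If the 40 moxibustion participants are treated in the order in which the text sets out the sessions, session and stimulated meridian are completely aliased in any Heart-session versus Lung-session comparison and in any same-site comparison at a midpoint. The within-session contrast of the Discussion is protected against a uniform session effect. It is not protected against site-specific carry-over at HT3 or the Heart midpoint, or against an order-by-site interaction, and one order cannot separate these from meridian specificity.

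The bias is −c/2 in the averaged midpoint contrast and 2p + c in a comparison of the two meridians' same-site effects. The sizes of p, c, g and k are not given, so the figures of 4.5 and 7 are illustrations only. The comparison of healthy controls with angina patients is unaffected; the point concerns 40 of 120 participants and one of the two hypotheses.

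**What to change.** In sections 2.6 and 2.6.1, state the session order and randomise the moxibustion group 1:1 to Heart-then-Lung or Lung-then-Heart. Include session and order in the repeated-measures analysis. Compare the 5-minute pre-moxibustion perfusion units between sessions at the two forearm midpoints, using recordings already planned. HT3 and LU5 each have a baseline in one session only, so a between-session check there would need a further probe. The device has four channels and three are used, but whether to add one is optional.

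A reader might infer that counterbalancing brings the bias to zero. That is true of period effects only. Carry-over becomes equal for the two meridians and estimable, but step 5 shows that it stays in the averaged contrast, so first-session results should be reported alongside.

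The cost is a short allocation list and about one degree of freedom for the session term (39 to 38; two-sided 5% critical t 2.023 to 2.024). No participants or visits are added, and the washout interval is left as it is. The article describes the trial as ongoing, so the list would apply to participants not yet treated, with the order actually used recorded and reported for the rest.
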